**Trial registration number:**

NCT01953510; Pre-results.

Strengths and limitations of this studyThis study is specifically designed to address two independent questions within a single study: which schedule to use for the provision of pneumococcal conjugate vaccine (PCV), and which PCV to use.This study includes a head-to-head comparison of the two licensed PCVs, allowing a direct assessment of their relative immunogenicity and impact on nasopharyngeal carriage.The primary outcome is the criteria used for the licensing and varying of PCV schedules.This study has relatively low power for the secondary nasopharyngeal carriage outcomes, so the ability to draw conclusions relating to these outcomes is vulnerable in the event of lower-than-anticipated carriage rates.

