## Methods and analysis

### Study setting

PCV introduction in Asia has been slow, in part due to a lack of local or regional data on the effect of PCV. We selected the Southeast Asian country of Vietnam as the location for the trial as a country with a strong health system, a track record of conducting relevant clinical trials, and a Government with strong interest both in the trial and in introducing PCV in the near future. Furthermore, trial results from Vietnam are likely to be considered as applicable to other countries in the region. This is the first trial involving infants to take place within Ho Chi Minh City, the largest city in Vietnam. The trial is conducted in two districts, District 4 and District 7. Districts are divided into communes, each of which has a health centre that provides preventive health services including EPI immunisations, along with some primary healthcare services. The study is conducted in one commune health centre in each district, with participants drawn from the surrounding communes within that district.

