### Sample size

The target sample size for infant recruitment (groups A–F) is 1200 with an allocation ratio of 3:3:5:4:5:4, resulting in target group sizes of A=150, B=150, C=250, D=200, E=250 and F=200. An additional target of 200 children aged 18 months are recruited into group G. Sample size calculations are based on the primary outcome of post-primary series immunogenicity (proportion of participants with serotype-specific antibody concentrations ≥0.35 µg/mL) for each of the two study questions. A non-inferiority margin of a 10% difference in absolute risk is deemed clinically significant, as used by regulatory authorities. Non-inferiority is assessed for each of the 10 serotypes in PCV10 (comparing groups A+B with group C or group E), and an overall conclusion of non-inferiority is drawn if the alternative hypotheses are accepted for at least 7 of the 10 serotypes. This sample size provides >99% power for the overall conclusion of non-inferiority with a 5% one-sided type I error rate, estimated by simulation using a tailor-made program written for implementation in Stata with 10 000 replications.^41^ Powers for serotype-specific hypotheses range from 83% to >99%, calculated in PASS Software 2002 using the Farrington-Manning (1990) method.^42^ Based on findings from our earlier work in Fiji and from data available in the literature,^43–45^ the assumed probabilities of antibody concentration ≥0.35 µg/mL are 95% for serotypes 1, 4, 5, 7F, 9V, 14 and 19F; 90% for serotype 18C; 80% for serotype 23F; and 75% for serotype 6B. The within-subject correlation between the multiple binary endpoints is captured by a subject-level variation term with SD 1.7 in a random-effect logistic regression model, and the loss to follow-up rate is assumed to be 5% post-primary series and 10% at 12 months of age. The sample size also provides 98% power to detect a difference in post-primary series immunogenicity following two doses of PCV10 or PCV13, defined by a 10% difference in absolute risk based on Fisher’s exact test (5% two-sided).

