### Allocation

The allocation sequence for groups A–F is produced using a computer-generated list of random numbers using a block randomisation scheme, stratified by district. The group allocation is contained within a sealed envelope at the study clinic, with sequential ID numbers written on the outside of the envelope. The allocation sequence is generated at Menzies School of Health Research. A study doctor will enrol participants and assign them to a study group by selecting the next available envelope. The envelope is not opened until after completion of the informed consent and eligibility assessment processes.

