### Statistical methods

#### Analysis of primary and secondary outcomes

For each of the two study questions, the primary objective is to compare a 2+1 schedule of (1) PCV10 and (2) PCV13, with a 3+1 schedule of PCV10. The primary outcome is the proportion of participants with serotype-specific antibody concentrations ≥0.35 µg/mL, 4 weeks post-primary series (at 5 months of age). Data from arms A and B are combined to form the three-dose post-primary series group. The primary analyses assess the non-inferiority of (1) two doses of PCV10 at 2 and 4 months of age (arm C) compared with three doses at 2, 3 and 4 months of age (arms A+B); and (2) two doses of PCV13 at 2 and 4 months of age (arm E) compared with three doses of PCV10 at 2, 3 and 4 months of age (arms A+B). The proportion of children achieving protective levels of serotype-specific IgG (≥0.35 µg/mL) 4 weeks post-primary series is determined for each of the 10 PCV10 serotypes. The non-inferiority margin is defined by a 10% difference in absolute risk. The serotype-specific risk differences (arms A+B/arm C) with 90% CIs are calculated using the Newcombe Score method and the null hypothesis rejected if the upper bound of the CI is <10%. Overall non-inferiority is declared if at least 7 of the 10 individual null hypotheses are rejected at a one-sided 5% level of significance. Secondary data analyses to address the primary objective include the ratio of GMCs post-primary series (arm C/arms A+B and arm E/arms A+B) with 95% CIs, and the booster response analysed by analysis of covariance, adjusting for pre-booster levels.

#### Analysis of key secondary objectives for study question 1

A single dose of PCV10 at 2 months of age (arm D) will be assessed for non-inferiority to three doses at 2, 3 and 4 months of age (arms A+B), as described for the primary objective.The impact of a booster dose on pneumococcal and NTHi carriage will be assessed at 12 months of age. Overall pneumococcal, capsular pneumococcal, PCV10 type and NTHi carriage rates will be determined. Proportions will first be compared between the 3+1 group (arm A) and the control group (arm F), using Fisher’s exact test. Where significant differences are found, rates will then be compared between the 3+0 group (arm B) and controls and between the 3+1 and 3+0 groups.

#### Analysis of key secondary objectives for study question 2

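### The 12-month carriage comparisons use an unstratified Fisher's exact test, an avoidable loss of about 4 to 6 points of power that a district-stratified score test would recover

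*Protocol article*

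**What the plan says.** All references are to the Protocol article.

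- **Allocation:** the sequence for groups A-F is generated "using a block randomisation scheme, stratified by district". Study setting gives the number of strata: "The trial is conducted in two districts, District 4 and District 7".
- **Statistical methods, key secondary objectives for study question 1:** for carriage at 12 months, "Proportions will first be compared between the 3+1 group (arm A) and the control group (arm F), using Fisher’s exact test". Arm B is compared with controls and with arm A only where A versus F is significant.
- **Statistical methods, primary outcome:** the risk differences "with 90% CIs are calculated using the Newcombe Score method". District is not mentioned there either.
- **Sample size, Carriage outcomes:** power is 76% (A versus F) and 71% (A versus B) for NTHi, and 64% and 59% for vaccine-type pneumococci. The basis is Fisher's exact test at one-sided 5%, a relative risk of 0.6, and control rates of 30% and 24%.
- **Strengths and limitations:** "This study has relatively low power for the secondary nasopharyngeal carriage outcomes".

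**The concern.** The randomisation uses district, but the test named for carriage does not. Fisher's test conditions on both margins and is discrete, so it spends only part of its nominal alpha at these sample sizes. The plan therefore names low carriage power as a limitation and then chooses a test that leaves about a quarter of the allowed type I error unused.

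Carriage is the trial's evidence on herd effect, which the Background says is mediated by carriage. The booster question (A versus B) is exposed twice, because it is reached only through a significant A versus F result. Power given up here could be recovered without another child, swab or visit.

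**Working it through.** **Inputs.** Sample size gives "resulting in target group sizes of A=150, B=150, C=250, D=200, E=250 and F=200" and "the loss to follow-up rate is assumed to be 5% post-primary series and 10% at 12 months of age". Evaluable at 12 months: A and B 150 × 0.9 = 135 each; F 200 × 0.9 = 180. Rates under the alternative: NTHi 30% versus 0.6 × 30% = 18%; vaccine type 24% versus 0.6 × 24% = 14.4%. Level: one-sided 5%, taken from Sample size because the analysis section gives no sidedness for carriage.

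**Step 1: reproduce the plan's figures.** Let x and y be the carriers in the two arms, with m = x + y. Fisher rejects when the hypergeometric probability P(X ≤ x | m) is at most 0.05. Power is the sum of the two binomial probabilities over the rejection region. The stated figures reproduce. Without the 10% loss the result is 80.6/75.0/69.1/63.2%, and with a two-sided 5% test 67.2/58.5/54.2/46.0%; neither fits.

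**Step 2: true size.** The same sum with both arms at the control rate gives 3.9% and 3.8% for NTHi, and 3.7% and 3.8% for vaccine type.

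**Step 3: change the test, without stratifying.** The uncorrected score test uses z = (x/n₁ − y/n₂) / √[p̄(1 − p̄)(1/n₁ + 1/n₂)] and rejects at z ≤ −1.645. Hand check for NTHi, A versus F:
- p̄ = (135 × 0.18 + 180 × 0.30)/315 = 0.2486
- null SE = √(0.2486 × 0.7514 × (1/135 + 1/180)) = 0.0492
- alternative SE = √(0.18 × 0.82/135 + 0.30 × 0.70/180) = 0.0475
- power ≈ Φ[(0.12 − 1.645 × 0.0492)/0.0475] = Φ(0.82) ≈ 79%

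Exact enumeration gives 79.5%, and the size of this test is 4.9-5.0% across the four comparisons.

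**Step 4: stratify by district.** With district k, Z = Σ(xₖ − n₁ₖmₖ/Nₖ) / √Σ[n₁ₖn₂ₖmₖ(Nₖ − mₖ)/(Nₖ²(Nₖ − 1))], without continuity correction. This was simulated with two districts of equal size. Control rates were either equal or at the planned rate ±10 points. The article gives no district rates, so that spread is an assumption.

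| Comparison | Stated | Fisher, exact | Score, unstratified | CMH, equal districts | CMH, ±10 points |
|---|---|---|---|---|---|
| NTHi, A vs F | 76% | 75.7% | 79.5% | 79% | 81% |
| NTHi, A vs B | 71% | 70.7% | 75.2% | 75% | 77% |
| Vaccine type, A vs F | 64% | 64.0% | 69.3% | 69% | 71% |
| Vaccine type, A vs B | 59% | 58.6% | 64.6% | 64% | 66% |

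The simulated size of the CMH test is about 5% at these rates. Changing the test alone gains 3.8, 4.5, 5.4 and 6.0 points. Stratifying adds nothing if the districts are alike and 1 to 2 points at ±10. At a wider assumed spread of ±50% of the mean rate, the total gain over Fisher is 6.6 to 8.0 points.

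**Step 5: put the gain in proportion.** The unstratified score test with 10% loss performs about as well as Fisher would with no loss at all (80.6/75.0/69.1/63.2%). For the gated booster question, take arm B at the control rate and arm A at a relative risk of 0.6. The chance of passing both A versus F and A versus B is then 60% for NTHi and 46% for vaccine type under Fisher, and 65% and 52% under the score test.

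**Step 6: size at low carriage.** With equal districts, the CMH test runs at about 5.5% at 5% carriage (135 versus 180) and about 6% at 3% carriage (135 versus 135). From 10% carriage upward it runs at about 4.8-5.1%.

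**Step 7: primary risk differences.** For serotype 6B at 75%, a district difference of 10 points (±5) cuts the variance by 0.05²/(0.75 × 0.25) = 1.3%. A difference of 20 points (±10) cuts it by 0.10²/0.1875 = 5.3%. Both spreads are assumptions.

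**The case against.** The plan is consistent with itself: it analyses carriage with Fisher's test, computes power with Fisher's test and discloses that power is low. An exact test is valid and guarantees its level at any carriage rate. The article names lower-than-expected carriage as its main risk, and that is where the asymptotic test can exceed 5%. All of this stands. It limits the point to efficiency and is why the fix needs a fallback.

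It is also fair that most of the gain has nothing to do with stratification. The change of test supplies it, and the district contribution rests on spreads that the article does not give.

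A reader might infer four stronger things that the document does not support:
- *The stated powers are wrong.* They are right for the planned test.
- *Ignoring the stratum inflates type I error.* The opposite happens: at an assumed ±50% spread, Fisher's size falls to about 2.9-3.3%.
- *The primary non-inferiority conclusion is at risk.* Overall power is stated as above 99%, a slightly wide interval is conservative for non-inferiority, and the variance at stake is small.
- *District is missing from the antibody concentration models.* The article is silent there, and that detail may properly sit in the analysis plan.

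**Conclusion.** The point holds as an avoidable loss of efficiency in the 12-month carriage comparisons. Fisher's test runs at about 3.7-3.9% instead of 5%, and replacing it with a district-stratified score test recovers about 4 to 6 points of power. A further 1 to 2 points depend on district differences of about ±10 points. These figures assume one-sided 5%, 10% loss, the planned control rates, a relative risk of 0.6 and two districts of equal size.

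The change reduces the low power but does not cure it: vaccine-type power remains about 64-71%. The A versus B figures are marginal, and the chance of reaching that conclusion through the gate is lower.

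**What to change.** - For the carriage comparisons, replace Fisher's exact test with the district-stratified Cochran-Mantel-Haenszel score test without continuity correction, and report stratified risk differences or ratios.
- State the sidedness and level in the analysis section, to match Sample size.
- Specify in advance that an exact or mid-p stratified test is used if observed carriage is about 5% or lower.
- Optionally, use a stratified Newcombe interval for the primary risk differences. This is consistent with the design but gains little.
- Do not plan a 2-month carriage covariate for NTHi: under Nasopharyngeal carriage outcome measures, no 2-month *H. influenzae* culture is planned in arms A and B. Such a covariate is available for pneumococcus only, and no gain from it has been calculated here.

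The cost is a few lines of text and code, settled before the carriage data are analysed. District is already recorded through the stratified allocation. The price is an asymptotic test in place of an exact one.

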The immunogenicity of two doses of PCV10 or PCV13 will be compared in relation to the proportion of participants with serotype-specific antibody concentrations ≥0.35 µg/mL (to the 10 shared serotypes), 4 weeks post-primary series (at 5 months of age). A significant difference will be indicated by a 10% difference in absolute risk, comparing PCV10 (arm C) with PCV13 (arm E), and an overall difference will be declared if at least 7 of the 10 individual null hypotheses are rejected and the seven differences are in the same direction.The immunogenicity of a single dose of PCV10 or PCV13 will be compared, as described for the immunogenicity of two doses.

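### The rule for comparing PCV10 with PCV13 uses the 10-point planning effect as its significance criterion, in conflict with the Fisher's exact test on which the comparison was powered

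*Protocol article*

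**What the plan says.** The rule is in the protocol article, Statistical methods, under the key secondary objectives for study question 2. The per-serotype criterion is "A significant difference will be indicated by a 10% difference in absolute risk, comparing PCV10 (arm C) with PCV13 (arm E"). The overall rule follows (its closing words, cut here, require one common direction): "an overall difference will be declared if at least 7 of the 10 individual null hypotheses are rejected and the seven differences are in the". The comparison of a single dose of PCV10 (arm D) with a single dose of PCV13 (arm E) is to be done in the same way.

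The Sample size section treats the same two-dose comparison differently. It claims "98% power to detect a difference in post-primary series immunogenicity following two doses of PCV10 or PCV13", with the difference "defined by a 10% difference in absolute risk based on Fisher’s exact test (5% two-sided"). There, 10 points is the effect to be detected and Fisher's exact test is the criterion.

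The same section gives the other planning inputs: group sizes ("resulting in target group sizes of A=150, B=150, C=250, D=200, E=250 and F=200"), attrition ("the loss to follow-up rate is assumed to be 5% post-primary series and 10% at 12 months of age"), response rates ("95% for serotypes 1, 4, 5, 7F, 9V, 14 and 19F; 90% for serotype 18C; 80% for serotype 23F; and 75% for serotype 6B") and correlation, through a random-effect logistic model ("The within-subject correlation between the multiple binary endpoints is captured by a subject-level variation term with SD 1.7").

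**The concern.** An effect size used for planning and a rejection criterion are different things. If 10 points is the effect to be detected, a test with good power rejects at observed differences well below 10 points. If 10 points is the threshold for the observed difference, a true difference of exactly 10 points crosses it only about half the time, whatever the sample size.

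The head-to-head comparison is listed among the trial's strengths, and the Introduction says no published study had directly compared post-primary series immunogenicity of the two vaccines. Observed differences between the smallest Fisher-significant value and 10 points change verdict according to which section is followed. If that choice is left until the data are seen, it could decide the conclusion.

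**Working it through.** **Inputs.** All are from the Sample size section except the 7-of-10 rule, which is from Statistical methods.
- 250 per arm (C and E) with 5% loss: 250 × 0.95 = 237.5, taken as n = 237.
- Higher-arm response rates: 95% (seven serotypes), 90%, 80% and 75%. Assumption: the other arm is 10 points lower for every serotype, since 10 points above 95% is impossible.
- Success: at least 7 of 10 serotypes meet the criterion in the same direction.
- Correlation: random intercept on the logit scale with SD 1.7, marginal rates held at the stated values. SD 0 means independent serotypes.

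**Step 1: the stated 98%.** Exact power of Fisher's test (5% two-sided) for one serotype is the sum, over all outcome pairs the test rejects, of Bin(x1; 237, p) × Bin(x2; 237, p − 0.10):

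| Rates | Fisher power |
|---|---|
| 95 vs 85 | 94.9% |
| 90 vs 80 | 84.1% |
| 80 vs 70 | 67.7% |
| 75 vs 65 | 62.6% |

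No listed rate gives 98%, so the figure fits an overall power. With independent serotypes, the chance that at least 7 of 10 reject (seven at 0.949, then 0.841, 0.677 and 0.626) is 98.4%. This reproduces the stated figure.

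**Step 2: the criterion as worded.** Count a serotype if the observed difference is at least 10 points. At n = 237 this needs 24 more responders (0.10 × 237 = 23.7). The expected excess when the true difference is 10 points is also 23.7, so the chance is close to one half; exactly, it is 51% at each of the four rates.

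With independent serotypes and p = 0.51:

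P(at least 7 of 10) = 120(0.51⁷)(0.49³) + 45(0.51⁸)(0.49²) + 10(0.51⁹)(0.49) + 0.51¹⁰ = 0.127 + 0.049 + 0.011 + 0.001 = 0.19

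Simulation with SD 1.7 (10,000 replicates) gives 30–31% at n = 237–238 and 33% at n = 250.

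**Step 3: where the two rules disagree.** Smallest observed difference that Fisher's test calls significant at n = 237:

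| Higher arm | Responders | Difference |
|---|---|---|
| 95% | 225 vs 212 | 13/237 = 5.5 points |
| 90% | 213 vs 197 | 16/237 = 6.8 points |
| 80% | 190 vs 170 | 20/237 = 8.4 points |
| 75% | 178 vs 157 | 21/237 = 8.9 points |

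Differences from these values up to 10 points count under the Sample size section and not under Statistical methods. For example, 225/237 vs 206/237 (95% vs 87%) differs by 19/237 = 8.0 points with Fisher p = 0.0036.

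In the other direction, enumerating every outcome at n = 237 and at n = 250 per arm found no observed difference of 10 points or more that Fisher's test fails to reject.

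**Step 4: correlation and the 98%.** Overall Fisher two-sided 5% power by simulation at n = 237 is 98.4% (SD 0), 97.9% (SD 0.5), 96.6% (SD 1.0) and about 94% (SD 1.7). With no loss (n = 250) and SD 1.7 it is 95.6%.

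**The case against.** The strongest reply is that the rule should be read with the Sample size section. The sentence that sets the 7-of-10 requirement speaks of null hypotheses being rejected, which implies a test, and the Sample size section names that test and its level for this comparison in similar words. On that reading 10 points is only the effect size and nothing is lost. This makes a Fisher reading plausible, and the 30% is the cost of following the sentence as worded, not evidence of what was intended. It does not remove the conflict, because the only per-serotype criterion in the rule is the 10-point difference. The primary non-inferiority analysis also uses 10% as a margin for rejecting null hypotheses, so a margin reading is possible too.

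A sponsor may also decline to call a difference below 10 points important. That is legitimate, but the article calls 10 points clinically significant only for the non-inferiority margin, and the sentence at issue defines a significant difference.

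Two stronger readings are tempting. A reader might infer that a bare cutoff inflates false positives because it ignores sampling error. For arms C and E it does not: every observed difference of 10 points or more is already Fisher-significant at the planned sizes. Under equal true rates at n = 237, such a difference has a probability of about 1.3% at 75%, 0.7% at 80%, 0.03% at 90% and below 0.001% at 95%. A reader might also infer that the 98% is a miscalculation. The article does not say that the SD of 1.7 was carried into that figure, or that the figure refers to the 7-of-10 rule, and it reproduces under independence.

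**Conclusion.** The concern holds as a conflict between two sections over a key secondary comparison. Taken literally, the rule has about 51% power per serotype and about 30% overall (19% to 33% across independence or SD 1.7 and n = 237 to 250), against the stated 98%. Under Fisher's test the overall power is about 94% to 98%, depending on correlation. These figures assume a true 10-point difference in one direction in all ten serotypes, starting from the listed rates. The consequence is lost power, and a conclusion that depends on which section is followed. The primary non-inferiority rule has its own interval method, bound and level, and is not affected.

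The point about the 98% is secondary and conditional. The figure appears not to carry the within-subject correlation stated in the same section. With SD 1.7 and 5% loss, overall Fisher power is about 94%. That is a question of stating the assumption, not an established error.

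**What to change.** In Statistical methods, key secondary objectives for study question 2, replace the 10-point criterion with: a serotype-specific difference between arms C and E is declared if Fisher's exact test rejects equal proportions at the 5% two-sided level. Keep the requirement for at least 7 of 10 rejections in the same direction, and say that 10 points is the planning effect only. Apply the same wording to the single-dose comparison of arms D and E. Naming Fisher's test matters because the power depends on it: an uncorrected chi-square test gives 96.3% at n = 237 with SD 1.7, not 94%.

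In the Sample size section, state the correlation assumption behind the 98%, or restate the figure as about 94% under SD 1.7 and 5% loss.

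The cost is wording in two sections. Sample size, visits and assays are unchanged.
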